#### Randomization procedures

Initially, all participants will be pooled into a single group. Afterwards, patients will be classified into quartiles by muscle thickness (MT) of *vastus lateralis* (VL) and type of critical disease and assigned in a random and counterbalanced way into one of the three training protocols: PM/control, BFRp, or BFRpE using a maximally tolerated imbalance model [47]. MT will be measured exclusively in the right leg. An unpaired *t* test will be used to ensure that there is no baseline difference between the groups. If significant between-group differences are detected, randomization will be repeated until a random distribution with no difference is achieved [48]. The Berger-Exner test will be applied to verify selection bias [49].

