#### Primary outcome measurements

##### Acute cardiovascular responses

The first training session (T1) will immediately succeed T0 and will have the monitoring of acute cardiovascular responses to training. Mean arterial pressure (MAP), central and peripheral systolic blood pressure (SBP [SBPc and SBPp]), and central and peripheral diastolic blood pressure (DBP [DBPc and DBPp]) will be measured by pulse wave analysis. Concomitantly, the heart rate (HR) and peripheral oxygen saturation (SpO_2_) should be recorded through a portable vital signal monitor (Dixtal, DX 2021, Amazonas, Brazil) every 2 min. The mean of 5 recordings at rest (10 min of rest), 18 recordings during exercise (~ 37 min of training), and the average of 5 post-exercise recordings (10 min) will be considered in the analysis. Electrocardiographic signals will be monitored, and, in case of adverse events, the session will be promptly interrupted. The training protocol will be applied to both legs during the session, simultaneously and alternately between the stimulated leg and the rest of the contralateral limb [37].

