#### Blinding procedures

To be considered a double-blind study, one of the authors will be assigned to create codes for the training-related adaptation data, in addition to being responsible for the randomization of patients. The evaluator, who evaluates the safety and training-related adaptations, will be blinded to the experimental groups. Each experimental group will be led by a different trainer who will also be blinded for the other training groups. Lastly, participants will be blinded by their coma, and in case the participant awakes from coma, information from the study will be provided, but not about the protocol they had previously undergone.

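### The pool, rank and redraw randomisation cannot be carried out with patients who enrol singly and start training straight after baseline; run as a batch, it would leave unadjusted p values conservative

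*Protocol article*

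**What the plan says.** The Randomization procedures section sets an order of steps. First, "Initially, all participants will be pooled into a single group". Patients are then put into quartiles of right-leg vastus lateralis (VL) muscle thickness and classified by type of critical disease. They are assigned to the three arms "using a maximally tolerated imbalance model". An unpaired t "test will be used to ensure that there is no baseline difference between the groups". Then comes the rule at issue: "If significant between-group differences are detected, randomization will be repeated until a random distribution with no difference is achieved". The section closes with a further check: "The Berger-Exner test will be applied to verify selection bias".

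The timing is fixed elsewhere in the article. Recruitment procedures places T0 within 23 h of ICU admission or coma identification. Under Acute cardiovascular responses, "The first training session (T1) will immediately succeed T0". Table 1 requires a predicted coma of 2 to 6 days. Sample size rationale gives 39 patients at 7.2 per month from a single ICU.

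Under Blinding procedures, "one of the authors will be assigned to create codes for the training-related adaptation data, in addition to being responsible for the randomization of patients". In Statistical analysis, the model contains group, time and subject, and names no baseline or stratification covariate. The Discussion presents the quartile stratification as a strength of the design. Trial status reports that the first participant was recruited in April 2020 and that recruitment was later suspended.

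**The concern.** Pooling, sample quartiles and between-group tests are properties of a complete cohort. This trial never has a complete untreated cohort, because each patient must be allocated on the day of enrolment. The written method therefore cannot be the one used, and the reader cannot tell what replaces it.

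Three things are at stake:
- **Concealment.** The only way to apply a repeat rule during accrual is to redraw the allocations still to come after looking at the baseline data so far. There is no cap on redraws and no stated safeguard.
- **Reproducibility.** One paragraph mixes a batch method with tools for sequential allocation, so the allocation mechanism is undefined.
- **Calibration.** Had redrawing been possible, the accepted allocations would be a selected subset of all allocations. Ordinary tests that ignore the balanced variables would not then have their nominal 5% level.

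**Working it through.** **Step 1. Feasibility.** The plan's accrual figure is 7.2 per month, which reproduces as 24 × 0.30.
- Time to assemble 39 patients: 39 / 7.2 = 5.4 months, in line with the stated minimum of 6 months.
- Mean gap between patients: 30.4 / 7.2 = 4.2 days.
- If the two stated losses are instead applied in sequence, 24 × 0.8 × 0.7 = 13.4 per month and 39 / 13.4 = 2.9 months. The conclusion is the same.

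Against this stand a 23 h limit for T0, training straight after T0, and a predicted coma of 2 to 6 days. When a patient must be allocated, the sample quartile limits are unknown and the final groups do not exist. When they do exist, every patient has been treated. The article gives no preset cut points, no batches and no sequential form of the repeat rule.

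**Step 2. Consistency within the section.** A maximally tolerated imbalance procedure limits the imbalance as patients are assigned in turn. The Berger-Exner test looks for selection bias arising from such a sequence. Neither fits drawing a whole cohort at once and redrawing it.

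**Step 3. How often the rule would be triggered.** Assumptions: equal arms of 13, normal data, simple randomisation, three pairwise two-sided t tests at 5%. By simulation, a sound randomisation fails at least one test on one baseline variable in about 12% of trials. For k independent variables the rate is 1 − (1 − 0.12)^k:
- k = 5: 1 − 0.88^5 = 47%
- k = 7: 1 − 0.88^7 = 59%

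The article does not list the variables tested, so k is an assumption.

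**Step 4. Size of nominal 5% tests if a batch could be run.** Null data for 3 × 13 patients were redrawn until all three t tests on one covariate had p ≥ 0.05. The size of later F tests was then measured. The correlation r between covariate and outcome is not in the document and is assumed. Ranges cover separate runs of about 4,000 to 53,000 accepted allocations; single values come from one run.

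| r | Post-only, unadjusted | Group by time (change) | Group main effect over both times | Adjusted for the covariate |
|---|---|---|---|---|
| 0.3 | 4.4–4.9% | 3.6–3.7% | 2.0–2.4% | 5.0–5.3% |
| 0.5 | 3.8–4.4% | 4.0–4.1% | 1.4–1.7% | 4.9–5.3% |
| 0.7 | 2.5–3.4% | 4.4–4.6% | 0.9–1.1% | 5.0–5.3% |
| 0.8 | 2.1–2.2% | 4.6% | 0.5% | 5.0% |
| 0.9 | 1.1–1.3% | 4.8–5.0% | 0.2–0.3% | 5.1–5.3% |

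No entry exceeds 5% beyond simulation error.

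**Step 5. The same with quartile balance on thickness.** Thickness then passes the t tests in practically every draw. The unadjusted post-only size is 2.2% at r = 0.5 and 0.7% at r = 0.7. Without any redrawing it is 2.4% and 0.6%. The loss therefore comes almost entirely from leaving the stratification factor out of the model. Adjusted for the covariate, the size is 4.6%.

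**The case against.** The best defence is that the section already names a valid sequential procedure, so the pooling language may be loose drafting around it. That supports a simple fix, but it does not rescue the text: the repeat rule is explicit and nothing in the article limits it.

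A second defence concerns consequence. This is a pilot, and the safety and applicability criteria are thresholds, not p values. That stands for the calibration point. It does not answer feasibility or concealment, because each protocol is judged on its own patients (for example, by the 15% limit on unsafe conditions), so how patients enter each arm still matters.

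The numbers also have fair limits. The correlations and the count of baseline variables are assumed. The 12% and the table use simple randomisation; under quartile balance the repeat rule would act mainly through variables other than thickness. Using t tests for three arms is a lesser matter, since Statistical analysis also names one-way ANOVA and Kruskal-Wallis at T0.

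Two stronger readings are tempting, and the document supports neither:
- A reader might infer that the rule makes the p values worthless or produces false positives. The error runs the other way, is modest for the group-by-time test, and disappears on adjustment.
- A reader might infer that allocation becomes aware of outcomes, because one author both randomises and creates the data codes. The check uses baseline data, a separate blinded evaluator measures outcomes, and creating codes is not said to involve seeing results. What remains is a risk to concealment, not a demonstrated breach.

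**Conclusion.** The point holds as an internal contradiction that must be resolved. The allocation method as written cannot be executed under the article's own timing, and it conflicts with the sequential tools named beside it. This conclusion needs no simulation and does not depend on the exact accrual rate. The concealment risk from redrawing during accrual is real but cannot be sized from the document.

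The effect on p values is secondary and hypothetical, since it arises only if a batch could be run. For tests that do not adjust for the balanced variables it is conservative. The post-only size falls from the nominal 5% to about 4 to 5% at r = 0.3 to 0.5 and about 1 to 2% at r = 0.8 to 0.9. The group-by-time test stays near 4 to 5%, while the group main effect falls further. These figures rest on 13 per arm, normal data, one tested covariate and simple randomisation. The cost is lost power in a small trial.

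**What to change.** - **Delete** the pooling step, the baseline t test and the repeat rule.
- **Allocate** each patient once, sequentially and concealed, with the maximally tolerated imbalance procedure already cited. Stratify by disease type; keep muscle thickness as a stratification factor only if its cut points are fixed in advance.
- **Adjust** every between-group model for T0 VL thickness (continuous) and disease type. Where VL thickness is itself the outcome, its T0 value should not serve as both covariate and response.
- **Separate roles.** Keep the allocation list with someone who neither codes nor analyses outcome data.
- **Patients already enrolled** since April 2020 keep their allocation, and the report states how they were allocated.

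The cost is revised wording, a new list for the remaining patients, two covariates from data already collected, and one reassigned task. Small chance imbalances will remain; the covariates handle them.

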#### Primary outcome measurements

##### Acute cardiovascular responses

The first training session (T1) will immediately succeed T0 and will have the monitoring of acute cardiovascular responses to training. Mean arterial pressure (MAP), central and peripheral systolic blood pressure (SBP [SBPc and SBPp]), and central and peripheral diastolic blood pressure (DBP [DBPc and DBPp]) will be measured by pulse wave analysis. Concomitantly, the heart rate (HR) and peripheral oxygen saturation (SpO_2_) should be recorded through a portable vital signal monitor (Dixtal, DX 2021, Amazonas, Brazil) every 2 min. The mean of 5 recordings at rest (10 min of rest), 18 recordings during exercise (~ 37 min of training), and the average of 5 post-exercise recordings (10 min) will be considered in the analysis. Electrocardiographic signals will be monitored, and, in case of adverse events, the session will be promptly interrupted. The training protocol will be applied to both legs during the session, simultaneously and alternately between the stimulated leg and the rest of the contralateral limb [37].

##### Cardiovascular safety and applicability of peripheral muscle training

To assess cardiovascular safety, HR values < 50 bpm or > 180 bpm, SBP < 80 mmHg or > 160 mmHg, DBP < 60 mmHg or > 80 mmHg, MAP < 60 mmHg or > 120 mmHg, cardiac or respiratory arrythmias, SpO_2_ < 88%, signals of respiratory discomfort [50, 51], or signals of deep venous thrombosis will be considered criteria to interrupt the protocol. Except for the occurrence of deep venous thrombosis, two consecutive training attempts will be performed after the first training interruption before withdrawing the patient from the study. It is suggested for two main reasons: to exclude the possibility of an occasional adverse event due to the variability of the clinical conditions, and to maintain the training frequency in case the patient continues in the study. In case of exclusion, the protocol will be considered unsafe for this patient. However, in case 15% or more unsafe conditions occur in the same training protocol, the protocol will be excluded from the study. To evaluate the applicability, the number of adverse events and intercurrence will be recorded, and if a total number of adverse events and/or intercurrence overcome 20% of the total training sessions, or there is deep venous thrombosis occurrence in at least 5% of the patients, protocols will be considered unsafe and impracticable. If cardiovascular variations are greater than 20% of the baseline, the protocol will be considered impractical.

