##### Passive mobilization associated with blood flow restriction protocol (BFRp)

A pressure cuff with 17.5 cm of width and 94 cm of length (JPJ, Sao Paulo, Brazil) with a pressure manometer will be placed on the quadriceps muscle, on the inguinal fold. Afterward, a vascular Doppler probe (DV-600; Martec, Ribeirao Preto, Brazil) will be placed in the posterior tibial artery. To determine the occlusion pressure, the cuff will be inflated until the auscultatory pulse stops [57]. An external compression of 85% of the total vascular occlusion pressure will be applied for 5 min, followed by a 3-min rest (compression release) [42]. The BFR protocol will be synchronized to the PM protocol. Compression will be repeated 5 times during the training session, and occlusion pressure will be re-evaluated in all sessions.

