### Cardiovascular assessment

#### Cardiovascular assessment by the pulse wave analysis

Pulse wave analysis will be performed using SphygmoCor equipment (SphygmoCor, AtCor Medical, Sydney, Australia). In a supine position, the patient will have a pneumatic clamp placed in the proximal portion of the left arm. Following that, additional data such as age, weight, and height will be provided to the system. After a 10-min rest, three measurements of systolic and diastolic arterial pressure will be performed in a 2-min interval [61] and accepted as long as the difference is less than 10% [62], or 5 mmHg [63] between the measurements. Afterward, the mean value of the three accepted measurements will be inserted into the system to obtain the MAP, SBPc, SBPp, DBPc, and DBPp [64–67]. In T0, the variables will be measured after 10 min of rest. In T1, it will be taken prior (10 min), during (23 and 37 min), and after (47 min) the training session. The average between minutes 23 and 37 (pause between sets) will be used as the exercise value.

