### Quality of life assessment

#### Quality of life using the SF-36 questionnaire

Quality of life will be assessed using the SF-36 questionnaire, an instrument of good acceptance, reliability, and validity for ICU patients validated in Brazil and easily administered by telephone [45, 46, 53, 54]. It comprises 8 domains: physical function, role-physical, bodily pain, general health, vitality, social functioning, role-emotional, and mental health. Scores range from 0 to 100, where 0 corresponds to the worst general health status, and 100 corresponds to the best health condition [86–88]. The categorization and description of the methods and analyses are shown in Table 2.

**Table 2 Tab2:** Categorization and description of the methods and analyses of the study variables

Evaluation category	Organic responses	Method of evaluation	Variables in analyses
Safety and applicability	Acute cardiovascular	Pulse wave analysis (PWA)	MAP, SBPc, SBPp, DBPc, and DBPp (mmHg)
Safety and applicability	Acute cardiovascular	Analyses of the vital signs	HR (bpm) and SpO_2_ (%)
Muscle systems	Muscle mass adaptation	Ultrasound image	Muscle thickness (cm)
Muscle systems	Muscle quality adaptation	Ultrasound image	Echo intensity (A. U. from 0 to 256)
Neuromuscular systems	Global muscle strength adaptations	Medical Research Council (MRC) Score	Number scoring (0 to 60)
Physical function	Adaptations in physical function in ICU	Physical Function in the Intensive Care Test Scored (PFIT)	Number scoring (0 to 12)
Physical function	Adaptations in physical functional performance after hospital discharge	Performance in the basic activities of daily living by the Barthel Index (BI) by telephone interview	Number scoring (0 to 100)
Clinical outcomes	Adaptations in quality of life	Medical Outcome Study 36 – Item Short Form Health Survey (SF-36) questionnaire	Number scoring (0 to 100)

*SBPc* central systolic blood pressure, *SBPp* peripheral systolic blood pressure, *DBPc* central diastolic blood pressure, *DBPp* peripheral diastolic blood pressure, HR heart rate, *MAP* mean arterial pressure, *SpO*_*2*_ peripheral oxygen saturation, *ICU* intensive care unit

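### At T1 the only pressure readings specified during training are at minutes 23 and 37, so on the best-fitting clock three of the five cuff releases have no specified pressure reading to set against the stopping limits

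*Protocol article*

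**What the plan says.** **Limits.** The section on cardiovascular safety and applicability lists the criteria for interrupting training: "To assess cardiovascular safety, HR values < 50 bpm or > 180 bpm, SBP < 80 mmHg or > 160 mmHg", followed by DBP below 60 or above 80 mmHg, MAP below 60 or above 120 mmHg, and criteria on rhythm, SpO2, breathing and thrombosis. It does not say which pressure reading, or at what time, the limits are judged on. A separate rule in the same section calls the protocol impractical if cardiovascular values move more than 20% from baseline.

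**Source of pressure.** Under Acute cardiovascular responses, MAP and the central and peripheral pressures "will be measured by pulse wave analysis". The monitor read every 2 min is given HR and SpO2. Table 2 repeats the split: in its safety and applicability rows, pulse wave analysis supplies "MAP, SBPc, SBPp, DBPc, and DBPp (mmHg") and the vital signs supply HR and SpO2.

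**Timing of pressure.** The section on pulse wave analysis states: "In T1, it will be taken prior (10 min), during (23 and 37 min), and after (47 min) the training session". It adds: "The average between minutes 23 and 37 (pause between sets) will be used as the exercise value".

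**Cuff cycle.** In the BFRp section, compression "will be applied for 5 min, followed by a 3-min rest (compression release"), and "Compression will be repeated 5 times during the training session". BFRpE adopts the same procedure. Both legs are trained, "simultaneously and alternately between the stimulated leg and the rest of the contralateral limb".

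**The concern.** The Background identifies the release of the cuff between sets as the event whose cardiovascular consequences are unknown, and cardiovascular safety is a primary objective. One would therefore expect a pressure reading soon after each release, at least in the session devoted to acute responses. The printed schedule instead places two in-session readings on a session with five releases.

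If that schedule is the only source of pressures, a short rise or fall confined to pressure after an unread release would not meet the interruption limits. It would then not enter the count of patients for whom the protocol is unsafe, nor the comparison with 20% of baseline. HR, SpO2 and ECG are followed throughout, so an excursion that also disturbs one of those can still be caught. The gap concerns the two cuff arms, because PM has no cuff.

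**Working it through.** **Inputs.** Five compressions of 5 min with 3-min releases (BFRp section). Session of 37 min (PM section). In-session pulse wave readings at minutes 23 and 37, and a post-session reading at minute 47 (pulse wave section).

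**Step 1: reproduce the session length.** 5 × 5 + 4 × 3 = 37 min, as stated. Recordings every 2 min: 37 / 2, rounded down, = 18. This matches the 18 exercise recordings given for the monitor.

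**Step 2: release times.** Release i falls at minute 5 + 8(i − 1), which gives 5, 13, 21, 29 and 37.

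**Step 3: match readings to releases.** Count a release as read if a specified reading falls 0 to 3 min after it. The 3 min is the length of the pause; the protocol sets no such window.

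| Clock | Release times on that clock | Read in session | Unread in session | Unread if minute 47 also counts |
|---|---|---|---|---|
| Starts with training | 5, 13, 21, 29, 37 | 3rd (by 23), 5th (by 37) | 3 of 5 | 3 of 5 |
| Starts with the 10-min rest | 15, 23, 31, 39, 47 | 2nd (by 23) | 4 of 5 | 3 of 5 |
| Training start, BFRpE cuff after its 5-min warm-up (assumed) | 10, 18, 26, 34, 42 | 4th (by 37) | 4 of 5 | 4 of 5 |
| Rest start, same BFRpE shift (assumed) | 20, 28, 36, 44, 52 | 1st (by 23), 3rd (by 37) | 3 of 5 | 2 of 5 |

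The training-start clock fits the text best. Minute 23 then lies in the pause from 21 to 24, minute 37 is the end of the session, and minute 47 is 37 + 10, the end of the post-exercise period. On this clock the releases at minutes 5, 13 and 29 are unread. The release at minute 37 counts as read only because a reading coincides with it; if that reading precedes deflation, 4 of 5 are unread.

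**Step 4: allow for triplicates.** The pulse wave section builds a value from three pressures taken 2 min apart, a span of 4 min. Successive pauses are separated by a 5-min compression, so one triplicate can touch only one pause. Two in-session readings therefore follow at most two releases, and at least 5 − 2 = 3 are unread in session on any of these clocks.

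**Step 5: another reading of the exercise value.** If the wording about minutes 23 to 37 means the two pauses in that stretch (21–24 and 29–32), releases 3 and 4 are read and 1, 2 and 5 are not: again 3 of 5.

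**Step 6: entry band against interruption band (mmHg; bpm for HR).**

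| | May start training | Interrupt |
|---|---|---|
| SBP | above 100 and below 150 | below 80 or above 160 |
| DBP | above 60 and below 100 | below 60 or above 80 |
| HR | above 60 and below 140 | below 50 or above 180 |

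For SBP and HR the entry band lies inside the interruption limits. For DBP it does not: a patient may start at 85 and already be over the upper limit.

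**The case against.** The strongest reply is that two purposes are being merged. Minutes 23 and 37 are set to obtain an exercise value for analysis, and Table 2 lists variables in analyses. The stopping limits read as a clinical list, and nothing says that only pulse wave pressures may trigger them. Patients in an ICU are likely to have bedside pressure monitoring, and a journal article may leave its device and interval to the full protocol. The entry conditions for training also presuppose a pressure from somewhere.

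Much of this stands. A reader might infer that blood pressure goes unmonitored after most releases; the document does not show that. A reader might also infer that later sessions have no pressure trigger because pulse wave analysis is scheduled only at T0 and T1. That rests on silence in a condensed article and is not part of this point.

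What remains is not silence. For T1 the article does fix a pressure source and exact minutes, under the label of safety and applicability, and these do not match the event it names as the hazard. The 18 exercise recordings do not fill the gap: they follow the sentence on HR and SpO2, while the pressure exercise value is built from minutes 23 and 37.

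It is also fair to say that no document gives the size or duration of a pressure change after release. A sustained or cumulative response could still appear at minute 23, 37 or 47.

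**Conclusion.** The point holds for T1 and is worth correcting. On the best-fitting clock, 3 of 5 releases have no specified in-session pressure reading, and 3 of 5 is the minimum for in-session readings on every clock examined. The counts are for one five-release sequence; if each leg has its own, there are up to 10 releases for the same two readings.

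Two stronger conclusions are not supported:

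- **That at least 3 of 5 releases lack any specified reading.** This is true only in session. With the post-session reading counted, some less likely timelines leave 2 of 5.
- **That the safety result is biased towards safe.** A missed excursion would lean that way, but only if the printed schedule is the sole source. The upper DBP limit pushes the other way, towards interruption. The net direction and size are unknown.

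The DBP conflict is a separate inconsistency between two stated rules and does not depend on the clock. The conclusion on releases assumes the cuff cycle runs as printed and takes the 3-min pause as the period in which a reading counts.

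**What to change.** 1. **Settle the DBP limits first.** Have the clinicians make the entry and interruption limits consistent. Otherwise a patient entering at 85 mmHg would be stopped at the first reading whatever the cuff did, and extra readings would multiply such stops.
2. **Keep the pulse wave readings** at minutes 23 and 37 unchanged for the central-pressure analysis.
3. **Add one pressure reading soon after each cuff release at T1**, from the bedside monitor or a cuff on the arm not used for pulse wave analysis. Time it to the actual release, and use the matching set-end times in PM so that the arms are observed alike.
4. **Name that reading** as the one on which the SBP, DBP and MAP interruption limits are judged at T1.

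**Cost.** Up to 5 readings per patient, 5 × 39 = 195 in all, or up to 10 per patient, 10 × 39 = 390, if each leg has its own sequence. Fewer are needed where the bedside monitor already records pressure at those times. More readings may also produce more interruptions.

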### Study population

The inclusion, non-inclusion, and exclusion criteria are shown in Table 1. All the criteria will be reevaluated before each training session, according to the clinical specificity of the criteria (Table 1). All non-included patients will be re-evaluated after 18 h of coma, except for patients whose hospitalization is longer than 18 h prior to ICU admission. In conclusion, all patients will be assisted by the ICU physiotherapy team. Additionally, the number of PM sessions or any type of physical therapy intervention in the peripheral muscle will be quantified to control the total volume of stimulus for each patient.

**Table 1 Tab1:** Inclusion, non-inclusion, and exclusion criteria of the study population

Inclusion criteria	Non-inclusion criteria	Exclusion criteria
1. Age of 25 to 55 years	1. Persistent arrhythmia with atrial fibrillation	1. Obese (BMI > 30 kg/m^2^)
2. Scores − 5 or − 4 according to the Richmond Agitation-Sedation Scale (RASS) or 3 to 5 in the Glasgow Comatose Scale	2. Pre-existing atrioventricular block or ventricular tachycardia	2. More than one thromboembolism risk factor
3. Maximal 18 h of coma in ICU admission or during critical care hospitalization	3. Recent acute myocardium infarction	3. Previous venous thrombosis and/or pulmonary embolism
4. Prediction of coma length between 2 and 6 days	4. Provisional or definitive pacemaker	4. Peripheral arterial vascular disease history or suspicion of lower limb arterial insufficiency
5. Prediction of 2 to 12 days of ICU permanence	5. Signals of intracranial hypertension	5. Severe cardiovascular instability and/or use of vasoactive drugs in infusion ≥ 0.5 mcg/kg/min
6. Daily protein consumption standardized for the ICU medical and nutrition teams	6. Neoplasia in chemotherapy treatment	6. Deep coagulopathy (prothrombin time (PT) > 2.5 times the normative values, activated partial thromboplastin time (APTT) > 2 times the normal or platelet count ≤ 50.000/μl)
	7. Non-consolidated fractures	7. Heparin intravenous infusion ≥ 2 UI/ml
		8. Fever or hypothermia
		9. Anemia
		10. Neurodegenerative disease
		11. Musculoskeletal disease

*ICU* intensive care unit

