### Study interventions

#### Peripheral muscle training

After T1, in view of the cardiovascular safety and applicability of PM, BFRp, and BFRpE, training sessions will be held twice a day, divided by 4 h [51]. The starting training leg will be randomly chosen at T1 and, from that, alternated in every training session. Patients will undergo the experimental protocol if they present controlled temperature (between 36.5 and 37.5 °C), stable blood pressure (> 100 and < 150 of SBP and > 60 and < 100 of DBP), SpO_2_ > 90%, respiratory rate (RR) < 25 rpm, and HR > 60 and < 140 bpm [55].

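### The upper diastolic limits conflict: a session may start at a DBP below 100 mmHg but must be interrupted above 80 mmHg, so an unchanged resting value can lead to an unsafe label

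*Protocol article*

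**What the plan says.** The section *Cardiovascular safety and applicability of peripheral muscle training* lists values at which a session is interrupted. For diastolic pressure these are "DBP < 60 mmHg or > 80 mmHg". They are absolute limits, with no exemption for a value present before the session began.

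The section *Peripheral muscle training* sets the conditions for undergoing a session, among them "stable blood pressure (> 100 and < 150 of SBP and > 60 and < 100 of DBP".

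Interruption starts a chain of consequences. Apart from deep venous thrombosis, "two consecutive training attempts will be performed after the first training interruption before withdrawing the patient from the study". One stated reason is "to exclude the possibility of an occasional adverse event due to the variability of the clinical conditions". If the patient is then withdrawn, "In case of exclusion, the protocol will be considered unsafe for this patient". At the level of the arm, "in case 15% or more unsafe conditions occur in the same training protocol, the protocol will be excluded from the study".

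The *Study population* section adds that "All the criteria will be reevaluated before each training session, according to the clinical specificity of the criteria". The criteria meant are those of Table 1, which contains no diastolic limit.

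**The concern.** A start rule should admit only patients who are not already at a stop limit. For DBP it does not. A patient resting at, say, 85 mmHg qualifies for training and meets the interruption criterion before the first movement.

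Cardiovascular safety is a primary objective, and the stop limits decide withdrawal, the patient-level unsafe label and the exclusion of a whole training protocol. If they can be triggered by a pressure that training did not alter, the absolute safety counts no longer describe the effect of training. This can happen in any arm, including the passive mobilization control.

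The repeat attempts do not protect against it. They are meant to filter out a chance event, and a stable resting value is not one: the same patient can be admitted and stopped each time. The same patient would also show 0% change under the separate criterion based on a 20% variation from baseline, so two safety criteria in one section would describe the same session in opposite ways.

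**Working it through.** **Inputs.** Start limits are from *Peripheral muscle training*, and stop limits are from *Cardiovascular safety and applicability of peripheral muscle training*. The total of 39 patients is from *Sample size rationale*. The plan gives no figure of its own to reproduce here.

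**Step 1: margins for every sign with both a start and a stop limit.** Lower margin = lower start limit − lower stop limit. Upper margin = upper stop limit − upper start limit. A negative margin is an overlap.

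| Sign | Start if | Stop if | Lower margin | Upper margin |
|---|---|---|---|---|
| SBP (mmHg) | > 100 and < 150 | < 80 or > 160 | 100 − 80 = 20 | 160 − 150 = 10 |
| HR (bpm) | > 60 and < 140 | < 50 or > 180 | 60 − 50 = 10 | 180 − 140 = 40 |
| SpO2 (%) | > 90 | < 88 | 90 − 88 = 2 | none set |
| DBP (mmHg) | > 60 and < 100 | < 60 or > 80 | 60 − 60 = 0 | 80 − 100 = **−20** |

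Only the upper DBP margin is negative. The overlap is 20 mmHg out of a start range of 100 − 60 = 40 mmHg, so 20/40 = 50% of its width. That is a share of the range, not of patients.

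**Step 2: does anything else in the text remove the overlap?** Table 1 has no DBP limit, so re-checking it before each session does not exclude 81–99 mmHg. The stop limits are not expressed relative to the resting value. The paragraph with the start limits opens by referring to the period after the first session (T1), so it is not explicit that they apply at T1. If they do, the conflict exists there too. If they do not, T1 has no stated DBP start limit and a patient above 80 mmHg can still be started.

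**Step 3: the path for an unchanged DBP of 85 mmHg.** Start rule: 60 < 85 < 100, met. Stop rule: 85 > 80, met. Change from rest: (85 − 85)/85 = 0%. First interruption plus two further attempts gives three in all. With the same resting value each attempt ends the same way, then come withdrawal and the unsafe label.

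**Step 4: how few patients reach the 15% rule.** The text does not state the denominator. Read per patient, with equal arms of 39/3 = 13: 0.15 × 13 = 1.95, so 2 patients, 2/13 = 15.4%. With 10 per arm: 0.15 × 10 = 1.5, so again 2 patients, 2/10 = 20%.

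**Step 5: illustration on assumed shares.** Let p be the share of patients who persistently rest above 80 mmHg, and suppose all of them are started each time. Then P(at least 2 of 13) = 1 − (1 − p)^13 − 13p(1 − p)^12:

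- p = 5%: 0.135
- p = 10%: 0.379
- p = 20%: 0.766

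The values of p are assumptions. The spread shows how strongly the result depends on a figure the article does not give.

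**The case against.** The strongest reply is that the start conditions and the stop list can be read together: staff would not begin a session in a patient who already meets a stop criterion. The working start range would then be 60 to 80 mmHg, and the cost would be missed sessions, not false unsafe labels. This is sensible bedside practice, but the text does not say it, and on that reading the start limit of 100 mmHg never operates. One of the two numbers is wrong either way.

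A second reply is that the path to the unsafe label is long: started in the overlap, interrupted, interrupted twice more, then withdrawn. That is true and is why the point is about what can happen, not how often. A third is that this is a pilot, the error is in the cautious direction, the control arm gives a concurrent reference, and the comparison of rest, exercise and recovery values is untouched. All of that stands and limits the weight of the point.

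Two stronger readings are tempting and not supported:

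- **A reader might infer that the lower limits conflict as well, since both are 60 mmHg.** They only abut. A DBP above 60 that does not change never falls below 60. Nor can a minimum margin be taken from the pulse wave section, where readings are "accepted as long as the difference is less than 10% [62], or 5 mmHg [63] between the measurements". That rule governs acceptance of replicate resting measurements, whose mean is then used; it is not stated as a tolerance for the stop limits.
- **A reader might infer that an arm is likely to be lost, or that the comparison between arms is biased.** The article gives no DBP distribution, the 15% rule is not stated per patient, and the overlap applies equally to all three arms.

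**Conclusion.** The concern holds for the upper DBP limit. As written, a resting DBP of 81–99 mmHg permits and interrupts the same session. The overlap of 20 mmHg follows directly from the stated limits and needs no assumption. That an unchanged value can end in withdrawal and an unsafe label assumes that staff apply the start rule literally and that the resting value persists over three attempts. That two patients can exclude an arm further assumes equal arms of 13 and a per-patient reading of the 15% rule. The frequency is unknown.

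This is a real inconsistency in rules that serve a primary objective, and it should be corrected. It inflates absolute safety counts and does not invalidate the trial.

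**What to change.** Set the upper DBP start limit below the upper stop limit, as is already done for SBP and heart rate. The preferred route is to lower the start limit to below 80 mmHg, because it leaves the safety limit as strict as it is now. The cost is fewer eligible sessions; the number cannot be estimated from the article. The alternative is to raise the stop limit above 100 mmHg. That loosens a safety limit in patients whose cardiovascular response the article itself calls unknown, so the investigators would need to justify it clinically. The exact values are their choice. A margin at the lower edge is optional.

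State that the start conditions also apply at T1.

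In the safety report, tabulate separately any DBP interruption whose pre-session DBP was already above 80 mmHg, and do not count it as training-related unsafe. This also covers patients already enrolled. It needs one extra line in a table and no new measurement where the pre-session DBP was recorded, since the start check already requires that reading.

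The first participant was recruited in April 2020, so this is an amendment to safety limits after enrolment began. *Trial status* reports a suspension of recruitment but not whether it has ended; the change should be made before further patients are trained.
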